#### Control: ECEC services and primary caregivers

ECEC services allocated to the control group will receive usual care, which includes the Munch and Move Programme. This programme is funded by the NSW government where health promotion support is provided to help ECEC services improve their nutrition and physical activity environments. While the programme includes support to improve breastfeeding environments, it does not target educator infant feeding and responsive feeding practices targeted in this study.^54^ Primary caregivers will have access to usual child and family health websites and government resources^53^ including webpages like the Raising Children Network and other freely available parenting resources; however, this will need to be actively sought out by parents. Parents will also be able to access child and family health services for routine developmental checks. To prevent contamination, the web-based online resources and training for ECECs will be accessible to intervention services only for the duration of the trial. The research team will manage the delivery of the caregiver intervention. Similarly, caregiver intervention resources are not publicly accessible and require a private link to ensure only intervention caregivers are accessing information.

### Outcome measures

#### zBMI

The primary outcome is child zBMI (measured twice at baseline and at 18 months follow-up (postintervention)). Measurements will be undertaken in an allocated area of the ECEC service by a research team member blinded to group allocation with appropriate child protection clearance and training in anthropometric measurement of infants.^55^ Research assistants will attend a 3-hour face-to-face training session facilitated by one researcher ([name]) to ensure familiarity with the data collection protocol. Children will be in light clothing, without shoes/jackets and with nappies on. Measurements will be completed following a standardised protocol for measuring infants.^56^ Weight will be measured with the child in a lying or seated position using a calibrated digital scale (Seca baby measuring scale, Model SE374) and recorded to the nearest 10 grams. Length will be measured with the child in a supine position on a level floor (with a Wedderburn Baby Measuring Mat Model WMHM110M) and recorded to the nearest 0.5 cm on a hard, flat surface. At follow-up, standing height will be measured barefooted using a mobile stadiometer (Charder HM 200P, in cm, to 10 mm increments). Two weight and length/height measurements will be taken at each time point. Where the measurements differ, a third measurement will be taken. The most common repeated measure will be used, or where all three measures differ, the average measure will be used.

#### Secondary outcomes

The following will be assessed at baseline and 18-month follow-up.

Primary caregiver outcomes

Duration of any breast milk. Caregivers will be asked about current and past breastfeeding to determine duration of breastfeeding (completed months) and exclusive breastfeeding to 6 months if applicable.Child variety and frequency of fruit and vegetable intake (daily) Intake (at home) will be assessed using items from a Food Frequency Questionnaire^57^ and the Children’s Dietary Questionnaire, which has been validated in children aged 2–5 years old.^58^ The variety, frequency and quantity of fruit and vegetables consumed by the child will be captured, and an overall score for variety and frequency will be calculated.Child frequency of consuming discretionary food and sugar-sweetened beverage intake (daily, weekly or monthly). Intake (at home) will be measured using eight items from the validated Food Frequency Questionnaire.^57^ This will capture the frequency of discretionary food consumption, specifically processed meats, biscuits, fried foods and sugar-sweetened beverages.Caregiver adherence to infant feeding recommendations and responsive feeding practices. Questions on infant feeding practices, developed by the research team, will assess the timing of introduction to solid foods and drinking from a cup, and general feeding style. Responsive feeding practices will be evaluated using an adapted version of the validated Feeding Practices and Structure Questionnaire.^59^ We will assess how often caregivers appropriately respond to hunger and satiety cues, engage in persuasive feeding or use food as a reward.^59^ Items will be measured on a 5-point Likert scale from never to always. The responses to each item will be summed to provide a score for each construct.

#### ECEC service outcomes

Comprehensive nutrition and breastfeeding policies. ECEC services will be asked to provide any infant and toddler nutrition/healthy eating or breastfeeding policies they adhere to. Policies will be reviewed and assessed for content from the NHMRC infant feeding guidelines,^14^ a statement of support for breastfeeding provided at first contact with families, documented feeding plans, responsive feeding practices and educator training.Educator infant and responsive feeding practices. Five items based on the adapted Environment and Policy Assessment and Observation (EPAO) tool^60^ exploring the frequency of a range of infant feeding practices for children aged 2 years and under will be asked to one nominated educator within the infant room. These practices are related to bottle feeding, using bottles or food to soothe children, encouraging children over 6 months to drink from a cup and use age-appropriate cutlery, as well as progressing food textures appropriately. They will be rated on a 7-point Likert scale from never to always. The educator will also be asked 14 questions exploring responsive feeding: (1) education/modelling (three items), (2) using food as a reward (four items), (3) mealtime environment (three items) and (4) use of coercive practices (four items). The items are rated on a 5-point Likert scale from never to always and are based on the Adapted About Feeding Children Strategies and Beliefs survey.^61^ The responses to each item will be summed to provide an overall score, as well as a score for each construct. At follow-up only, we will also undertake researcher observations during a main mealtime, where most children are present (typically lunch) to assess delivery of the targeted feeding practices using an adapted version of the EPAO previously employed by the research team.^62^

#### Intervention cost (cost-effectiveness outcome)

Costs associated with initial intervention development and intervention delivery/implementation will be recorded by the research team and collected via REDCap throughout the study period. Development costs related to the web-based platform, suite of text messages, training modules and resources will be documented by the research team via REDCap. Direct costs for intervention delivery will include staff time (ECEC staff, HPOs, administrative support), expert fees for webinar delivery, physical resource provision, website maintenance, text-message and e-newsletter platform expenses, and training and ongoing support to educators. Both will be documented by the research team via REDCap. ECEC educators will report on staff time and resources used on infant nutrition via the survey at baseline and follow-up. For primary caregivers, costs will be measured by estimating the time spent engaging with the intervention materials. This will be captured through website software analytics and by estimating time required to complete education modules if accessed. Similarly, primary caregivers will be asked to estimate how much money and time they spend feeding their child at baseline and follow-up to allow for comparisons between groups.

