### Study treatments

#### Intervention: ECEC services

To support implementation of the targeted practices outlined in figure 2, we will employ the following strategies facilitated by a health promotion officer located within HNELHD. This will be delivered to a nominated educator within the infant room and the service manager. ECECs will:

Complete the web-based Tiny Bites self-assessment to develop an action plan for implementation. The self-assessment questions relate to having comprehensive policies for breastfeeding, infant feeding and responsive feeding, providing regular and accurate communication as well as resources to primary caregivers around infant feeding and responsive feeding and supporting educators with implementing best practice responsive feeding practices.Attend an initial educational outreach visit by the health promotion officer and receive three to four support calls throughout the intervention (facilitation) to support self-assessment, action planning and address any barriers to implementation.Appoint a Nutrition Champion for the infant room who will act as the point of contact for the Tiny Bites programme at the service driving implementation, guiding staff, modelling responsive feeding practices and engaging families.Receive educational resources to support policy and practice change (eg, policy and orientation templates, hard copy resources, checklists and posters) as well as resources to support regular parent communication.Receive access to online professional development including six 15 min self-paced webinars covering infant feeding and responsive feeding practices; and one 35 min self-paced webinar covering nutrition conversations with caregivers.

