#### Intervention: primary caregivers

Primary caregivers in the intervention arm will receive:

Regular text messages (up to 74 over an 18-month period) tailored to their child’s age (from age 4 to 36 months, depending on age at enrolment).Monthly e-newsletters via email summarising resources and SMS message content (these newsletters will also be delivered to nominated individuals who may be involved in feeding children, such as grandparents/extended family members). Some SMS messages and digital newsletters will include prompts to reach out to ECEC educators to discuss any changes in their child’s diet or feeding.Access to a digital toolbox which houses a codesigned evidence-based collection of infant feeding and responsive feeding resources called the Lumpy Road to Solids, situated on the The Grow & Go Toolbox website funded by the Australian Government. Some SMS messages and e-newsletters will include links that direct caregivers to this webpage and/or specific resources.Access to the infant feeding and responsive feeding webinars developed to support ECECs with implementation (see above for more detail).

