### Process evaluation measures

The following evaluation measures will be reported on at follow-up.

Engagement: We will track access and use of the web programme by ECEC services using website analytics (eg, number of webinar views). The completion status of the action plan for each service will be monitored. We will also record the number of primary and secondary caregivers interacting with monthly e-newsletters (eg, open/click rate) and accessing embedded resource links (ie, Lumpy Road to Solids website and resources). Finally, we will report the number of text messages successfully delivered.Acceptability: Intervention ECEC managers and educators will be asked to report on the acceptability of the intervention using four items based on the validated Acceptability of Intervention Measure tool.^64^ Caregivers will be asked to assess the acceptability of the intervention components using measures developed by the research team.Feasibility: Feasibility will be assessed with ECEC services via a survey using four items (three questions on a Likert scale and one open-ended item) adapted from the Feasibility of Intervention measure.^64^Fidelity: Fidelity of HPO implementation strategies within ECEC services will be measured using monitoring instruments within REDCap.

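### The methods named for measuring caregiver time do not cover reading the texts and e-newsletters, so caregiver cost is understated in the widest cost perspective if they are followed as written

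*Protocol article*

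**What the plan says.** In the protocol article, the section Intervention cost (cost-effectiveness outcome) sets the quantity to be measured: "For primary caregivers, costs will be measured by estimating the time spent engaging with the intervention materials". The next sentence gives the method: "This will be captured through website software analytics and by estimating time required to complete education modules if accessed".

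The section Intervention: primary caregivers lists four components:

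- "Regular text messages (up to 74 over an 18-month period) tailored to their child’s age"
- "Monthly e-newsletters via email summarising resources and SMS message content"
- a web-based toolbox of feeding resources
- "Access to the infant feeding and responsive feeding webinars developed to support ECECs with implementation"

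The same section says that only some of the texts and newsletters carry links to the web resources.

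Under Process evaluation measures, engagement data include the number of caregivers "interacting with monthly e-newsletters (eg, open/click rate) and accessing embedded resource links". For the texts the section says: "Finally, we will report the number of text messages successfully delivered". Neither measure is tied to the cost calculation.

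The Economic evaluation section presents costs from three perspectives: the health service alone, the health service with ECEC services, and both of these with primary caregivers. Caregiver time enters only the third.

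**The concern.** The quantity is defined broadly, as time with all the materials, and the stated means of measuring it are narrower. Web analytics and module time fit the two components that a caregiver must choose to open. They do not fit the two that are sent to every intervention caregiver. A text or emailed newsletter that is read without following a link leaves no trace in either source.

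Only the intervention arm receives these items, so any reading time left out lowers incremental cost in one direction. In the third perspective, for any given reduction in zBMI, the cost per 0.1 zBMI would look more favourable than the article's own definition of caregiver cost implies.

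**Working it through.** The article states no figure for caregiver time or cost, so there is nothing to reproduce. The check has two parts: coverage, then scale.

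**Coverage.** Each caregiver component set against the two named methods:

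| Component | Web analytics | Module time | Other data in the article |
|---|---|---|---|
| Texts (up to 74) | only visits that follow a link | no | number delivered (engagement) |
| Monthly e-newsletters | only visits that follow a link | no | open/click rate (engagement) |
| Web toolbox | yes | not applicable | link access (engagement) |
| Webinars | possibly | yes | webinar views tracked for ECEC services |

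Two other items in the cost section might seem to fill the gap, but do not. The caregiver survey question concerns money and time spent on feeding the child, which is a different quantity. The platform expenses for texts and newsletters are counted, but as a delivery cost and not as caregiver time.

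**Scale.** Inputs from the article:

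- Texts: at most 74 over 18 months.
- Newsletters: monthly for 18 months, so about 18.
- Webinars: "six 15 min self-paced webinars covering infant feeding and responsive feeding practices", so 6 × 15 = 90 minutes if all are completed.
- Intervention caregivers: 270 (Sample size calculation).

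The unit reading times are not in the documents. I assume 0.25 to 1 minute per text (t) and 1 to 5 minutes per newsletter (n).

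Uncounted minutes per caregiver, if every item is read = 74 × t + 18 × n:

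- Low (0.25, 1): 18.5 + 18 = 36.5 min
- Middle (0.5, 2): 37 + 36 = 73 min
- High (1, 5): 74 + 90 = 164 min

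Over the arm, minutes × 270 / 60 gives about 164, 329 and 738 hours.

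Relative to the 90 minutes of webinars, the ratios are 36.5/90 = 0.41, 73/90 = 0.81 and 164/90 = 1.82. The uncounted part is therefore of the same order as the largest module time that could be counted.

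These totals fall in proportion to the share of items read. If half are read, the range is 18.25 to 82 minutes. Since 74 is a maximum, a caregiver sent fewer texts would also have less.

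**The case against.** The strongest case on the other side has five parts.

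- **The list is not called exhaustive.** A reader might infer that reading time is costed at zero. The article does not say so. It neither says that these are the only two sources nor assigns a value to reading time, and the sentence that defines the cost is wide enough to include texts and newsletters. This stands, and the point should not be put that way.
- **Unit times belong in a fuller economic plan.** Minutes per message are the kind of detail that an article leaves out, and their absence alone would be no finding. This stands only in part. The article is not silent. It states a method, and the method does not reach the quantity that it is meant to measure.
- **No data are lost.** Deliveries and newsletter opens are already recorded, so reading time can be added at analysis. This stands. It makes the remedy cheap, but does not show that the remedy is planned.
- **The consequence is limited.** A reader might infer that the whole cost-effectiveness result is biased. The documents do not support that, because costs are reported separately by perspective and caregiver time enters only the third. If feeding time and money also enter that perspective, a difference between arms there could run either way and could outweigh reading time. No share of total programme cost can be derived, because the article gives no cost figures.
- **Delivered is not read.** Multiplying every delivered text by a reading time would tend to overstate caregiver time. This stands, and the fix has to allow for it.

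**Conclusion.** The point holds in a limited form. The two named methods fall short of the article's own definition of caregiver cost, because neither measures reading of texts or emailed newsletters and no other stated item does. Followed as written, this understates incremental caregiver cost in the perspective that combines health service, ECEC services and caregivers. The other two perspectives and the zBMI analysis are untouched.

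The size cannot be taken from the documents. The range of about 37 to 164 minutes per caregiver over 18 months rests on assumed unit times, on all 74 texts and 18 newsletters being received, and on all of them being read. It is an amount of time, not a proportion of programme cost. A claim that a given percentage of caregiver time is missed would need further assumptions about module uptake and web use, and the article offers no basis for them.

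**What to change.** In the Intervention cost section, or in the economic analysis plan that it feeds, define caregiver time as the sum of:

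- web time from analytics;
- module time, if accessed;
- texts delivered × an assumed probability of reading × a fixed reading time per text;
- e-newsletters opened × a fixed reading time per newsletter.

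Take deliveries and opens from the engagement data. Totals for the intervention arm are enough for a mean cost. Count primary caregivers' opens separately from those of other recipients, and let the unit times exclude time on linked pages, which web analytics already capture.

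Set the unit times and the reading probability before results are known. In the third perspective only, run a sensitivity analysis that varies the unit times and takes the text-reading probability from zero to all delivered texts read. The upper end is a bound, since delivery does not show reading.

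The cost is a few sentences and three assumed inputs, with no new data collection. The downside is that these inputs are assumptions and that the cost per 0.1 zBMI in that perspective becomes slightly less favourable.

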#### Economic evaluation

To determine cost-effectiveness, the total cost of the intervention will be presented disaggregated for varied stakeholders including: (1) the health service alone, (2) health and ECEC services and (3) health+ECEC services+primary caregivers. The total costs will also be estimated with and without the cost of intervention development (assuming the intervention is in steady state). The incremental cost of the intervention (cost of intervention–cost of usual care) will be calculated. A cost–consequence analysis will be conducted, presenting incremental costs of the intervention along with the differences in all outcome measures. Cost-effectiveness analyses will present the additional cost per 0.1 zBMI reduction. The long-term benefit of improvements in child zBMI will be modelled to longer term outcomes (health adjusted life years gained) using a previously developed and validated proportional multistate, multiple cohort lifetable model.^63^

#### Adverse effects

In services where food is provided, ECEC managers will be asked about the percentage of food wastage for children aged 2 years and under, and the number of complaints or concerns raised by caregivers and staff around infant feeding and nutrition at baseline and follow-up. Questions will be developed by the research team.

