### Objectives

This cluster RCT aims to assess the efficacy of ‘Tiny Bites’, an 18-month digital health intervention delivered to ECEC educators and primary caregivers of children aged 4 to ≤12 months, relative to a usual care control group on child zBMI scores (primary outcome). We also sought to assess the impact of the ‘Tiny Bites’ programme at 18-month follow-up on:

Duration child receives any breastmilk.Child consumption of fruits and vegetables, ‘discretionary’ foods and consumption of any sugar sweetened beverages.Primary caregivers’ implementation of recommended infant feeding practices (as outlined in the Australian Infant Feeding Guidelines) and evidence-based responsive feeding behaviours.ECEC implementation of comprehensive nutrition and breastfeeding policies and adoption of evidence-based feeding recommendations including responsive feeding.Costs associated with intervention development, delivery and implementation.Cost-effectiveness of the intervention, expressed as the additional cost per 0.1 zBMI reduction.Potential adverse effects of the intervention (eg, food wastage, caregiver/ECEC staff complaints).Process evaluation measures including intervention engagement and acceptability (as reported by ECEC services and caregivers), and feasibility and fidelity (from the perspective of ECEC services).

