### Blinding

ECEC services and caregivers will not be blinded to group allocation. Where possible, data collectors for the primary outcome data will be blinded; however, due to the nature of the intervention, it is possible that some elements of the intervention (ie, posters displayed at the service) may be visible to data collectors at follow-up. The statistician will be blinded to group allocation.

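### The adverse-effect count combines complaints with concerns about infant feeding, and only the intervention arm is prompted to discuss feeding with educators, so an arm difference cannot be cleanly read as harm

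*Protocol article*

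**What the plan says.** Among the objectives at 18 months, the Objectives section of the protocol article lists: "Potential adverse effects of the intervention (eg, food wastage, caregiver/ECEC staff complaints". Complaints are the only example there that concerns what caregivers or staff say.

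The Adverse effects section, under Outcome measures, sets two measures, both reported by service managers. One is the percentage of food wasted. The other is "the number of complaints or concerns raised by caregivers and staff around infant feeding and nutrition at baseline and follow-up". The section describes no separation of complaints from concerns, no attribution to the programme and no treatment of contact that the programme itself prompted. It ends: "Questions will be developed by the research team".

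Four other places bear on this count:

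- Intervention: primary caregivers. Some text messages and newsletters "include prompts to reach out to ECEC educators to discuss any changes in their child’s diet or feeding".
- Intervention: ECEC services. Services receive resources for regular communication with parents, and the professional development includes "one 35 min self-paced webinar covering nutrition conversations with caregivers".
- Control. Caregivers have the usual websites and government resources, but "this will need to be actively sought out by parents". No study prompts are described for this arm.
- Blinding. "ECEC services and caregivers will not be blinded to group allocation". The managers who supply the count therefore know their allocation.

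**The concern.** A complaint expresses dissatisfaction. A concern may be no more than a question about a new food or texture, which is the kind of conversation the programme tries to encourage. The article itself treats communication between services and caregivers as a likely mechanism of effect and measures it separately. If some of these conversations are recorded as concerns, the same event supports the mechanism in one table and counts as an adverse effect in another, and the programme stimulates it in one arm only. This is differential ascertainment arising from how the outcome is defined.

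Two readings are at stake. A higher count in the intervention arm could be engagement, harm or both. A real change in complaints could also be blurred by a change in ordinary feeding concerns. The difference is likely to be shown to decision-makers: the Economic evaluation section plans a cost-consequence analysis that sets incremental costs beside the differences in all outcome measures, and Adverse effects sits under that heading. The count is also one of only two measures in the Adverse effects section.

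**Working it through.** The plan gives no rate, expected count or power figure for this measure, so there is no figure of its own to reproduce. Its sample-size calculation concerns zBMI and does not enter here. The check has two parts.

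**1. What the combined count can identify.** Write the arm difference at follow-up as D = (difference in complaints) + (difference in other concerns). Only D is observed, so the two terms cannot be separated. Subtracting baseline does not help: the prompts start after allocation and in one arm only, so whatever they add remains in the difference between the arms' changes from baseline.

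**2. How large the effect could be, under assumed rates.** Inputs:

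- 30 services per arm (60 services randomised 1:1; Sample size calculation and Randomisation).
- λ = true complaints per service, equal in both arms, so there is no harm. Assumed 1, 2 or 4.
- a = extra concerns recorded per intervention service because of the prompts. Assumed 0.25, 0.5 or 1.0.
- Poisson counts (assumed).

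Apparent rate ratio RR = (λ + a)/λ, and z = ln(RR) / √[1/(30(λ + a)) + 1/(30λ)].

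| λ | a = 0.25 | a = 0.5 | a = 1.0 |
|---|---|---|---|
| 1 | RR 1.25, z 0.9 | RR 1.50, z 1.7 | RR 2.00, z 3.1 |
| 2 | RR 1.13, z 0.7 | RR 1.25, z 1.3 | RR 1.50, z 2.4 |
| 4 | RR 1.06, z 0.5 | RR 1.13, z 0.9 | RR 1.25, z 1.8 |

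Every ratio exceeds 1 only because a was added and nothing was subtracted. If better communication also removes b concerns per service, then RR = (λ + a − b)/λ. With λ = 2 and a = 0.5, b = 0.5 gives (2 + 0.5 − 0.5)/2 = 1.00, and b = 1.0 gives (2 + 0.5 − 1.0)/2 = 0.75. Here λ stands for all complaints and concerns that would arise without the programme.

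The table therefore shows that modest extra reporting could matter. It does not estimate how much there will be. Variation between services beyond Poisson would lower the z values, as would a smaller number of reporting services.

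**The case against.** The strongest reply is that several steps lie between a prompt and a counted event. The prompt asks caregivers to talk to educators about changes, which need not be a concern at all. The count comes from managers, so the conversation must reach the manager, be recalled, and be classed as a complaint or concern. A reader might infer that intended engagement will be scored as harm. The documents do not support that; they support only that it may be.

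A reader might also assume that the distortion must run against the intervention. That is not supported either, because trained educators and regular communication could reduce the concerns that reach managers. Nor can a number of spurious events be derived from the planned caregiver numbers: no response rate is given, and the section opens by referring to services where food is provided, which may restrict who answers.

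Three further replies carry some weight. The examples in the Objectives are an open list, so adding concerns contradicts nothing. Recording concerns broadly is a defensible way to pick up unease that never becomes a complaint. And the questions were still to be written, so the survey may already separate the two.

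These replies lower the importance of the point but do not remove it. The measure as stated is one number, the prompting is confined to one arm, and the reporters are unblinded. Keeping concerns in view does not require pooling them with complaints.

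**Conclusion.** The point holds as a minor one. As described, the count is open to differential ascertainment, and a difference between arms may partly reflect engagement that the programme intends. The size and the net direction are not computable from the documents; the rate ratios above rest wholly on assumed rates.

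A reader might conclude that the safety objective cannot be answered. That goes too far. Food wastage is measured as well, any serious adverse event is to be reported to the ethics committee, and the separate communication measures give some context for reading a rise. The supportable conclusion is that this one count cannot be cleanly interpreted as harm. No primary inference, sample-size figure or main analysis depends on it.

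**What to change.** At follow-up, ask managers in both arms, in identical wording, for two separate numbers:

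- (a) Complaints, meaning dissatisfaction or objection about feeding practices or the programme. Report these as the adverse effect named in the Objectives.
- (b) Other feeding concerns or questions raised. Report these separately, read alongside the measures in Communication between ECECs and caregivers.

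Keep the combined total as well. Baseline was scheduled for July to September 2024, before the date of this protocol version (22 October 2024), so the pooled item may already have been asked, and the total preserves that comparison. Concerns should stay in the report, since dropping them would lose sensitivity to unease that is never voiced as a complaint.

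The cost is one extra line in a survey whose questions the team writes itself. The downside is that managers must sort what they recall into two categories, with some misclassification likely.
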